### Primary Outcomes

Primary performance outcomes include the TUG, the 3XF8W, and the Four Square Step Test. Assumptions of normality and homogeneity will be tested. If met, a multivariate analysis of variance (MANOVA) will be used to evaluate the effect of foot configuration at α=.05. A permutational MANOVA will be used if assumptions are violated. If multivariate differences are significant, post hoc paired *t* tests (or Wilcoxon signed-rank tests if nonnormality is present) will be used to assess individual outcomes without correction for multiple comparisons. In order to help control the familywise type I error risk, pairwise comparisons of the primary outcomes will only occur if the multivariate difference comparison from the MANOVA is significant.

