### Power

With n=30 for the above-knee and K2 groups, the study is powered (>80%) to detect a standardized effect size of 0.53. In the bilateral group (n=16), the power is greater than 50% for the same effect size. Preliminary data show larger effects (eg, 0.98 for the 3XF8W), supporting adequate power. Although underpowered to detect a meaningful difference in the bilateral group, 16 subjects is in line with other gait studies that have published data on 10 [13], 15 [14], or 19 [15] subjects with bilateral amputations, a challenging population to recruit and enroll. The study is also powered (81%) to detect a 75% preference for one configuration (vs 50% under the null) using a sign test with n=30. Although no minimal clinically important difference has been established, it is predicted that a standardized effect of at least 0.50 will correspond to an impactful improvement in participants’ physical function.

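### The MANOVA gate holds the familywise error of the three primary follow-up tests only when no outcome differs; if exactly one differs, the error for the other two is about 6 to 10%

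*Protocol article*

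**What the plan says.** The section Primary Outcomes in the protocol article fixes the rule. The family has three members: "Primary performance outcomes include the TUG, the 3XF8W, and the Four Square Step Test". The global test is a "multivariate analysis of variance (MANOVA) will be used to evaluate the effect of foot configuration at α=.05", with a permutational version if assumptions fail. If it is significant, paired t or Wilcoxon tests "will be used to assess individual outcomes without correction for multiple comparisons". The purpose of the gate is stated: "In order to help control the familywise type I error risk, pairwise comparisons of the primary outcomes will only occur if the multivariate difference" is significant. No Holm, Bonferroni or closed-testing step is named.

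Two neighbouring sections treat multiplicity differently. Satisfaction Measures lowers alpha to .025 so that the familywise rate stays at .05. Secondary Outcomes applies no correction but labels the results exploratory. Under Statistical Analysis, all analyses are run separately in each amputation group, so the rule applies within each group.

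The section Power states: "With n=30 for the above-knee and K2 groups, the study is powered (>80%) to detect a standardized effect size of 0.53". For the bilateral group it states: "In the bilateral group (n=16), the power is greater than 50% for the same effect size". It also reports: "Preliminary data show larger effects (eg, 0.98 for the 3XF8W), supporting adequate power".

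**The concern.** A global test followed by uncorrected tests gives weak control of the familywise error: it protects when every null hypothesis is true. With three outcomes there is a gap. To claim one outcome with strong control, closed testing requires rejection of the three-outcome null, both two-outcome nulls that contain it, and its own null. The plan tests the first and the last and skips the two-outcome nulls. When one outcome truly differs, the joint null of the other two is true but never tested, and each of the two gets its own test at .05.

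At stake are claims on individual primary outcomes, for example that the unlocked foot improves the TUG as well as the 3XF8W. The global MANOVA conclusion is not affected.

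**Working it through.** **Inputs from the article.** Three outcomes; gate at .05; follow-up tests uncorrected (read as .05 each, two-sided); n=30 (above-knee, K2) and n=16 (bilateral); effects 0.53 (power) and 0.98 (preliminary 3XF8W).

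**Assumed.** Correlation between the three within-person differences, not given, is varied from 0 to 0.9. Differences are normal.

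**1. The stated power.** For a single paired t test at two-sided .05, the noncentrality is d√n.
- n=30: 0.53 × √30 = 2.90, power 80.1% (stated: above 80%).
- n=16: 0.53 × √16 = 2.12, power 51.0% (stated: above 50%).

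Both figures reproduce, but only as one uncorrected paired t test with no gate.

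**2. Closed-form limits.** With independent outcomes and no gate, three null tests give 1 − 0.95³ = 14.3%. With one true effect so large that the gate always opens, the two remaining null tests give 1 − 0.95² = 9.75%.

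**3. Simulation of the plan's rule** (60,000 runs per setting, simulation error about 0.1 point). For paired data the MANOVA is Hotelling's T² on the three differences: T² = n·d̄ᵀS⁻¹d̄, and (n−3)T²/[3(n−1)] is compared with F(3, n−3). Three paired t tests at .05 follow if it is significant. Chance (%) of at least one false claim, by correlation:

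| Outcomes that truly differ | n | 0 | 0.3 | 0.5 | 0.7 | 0.9 |
|---|---|---|---|---|---|---|
| none | 30 | 4.7 | 4.3 | 3.8 | 3.2 | 2.7 |
| none | 16 | 4.2 | 4.0 | 3.5 | 3.2 | 2.6 |
| one, at 0.98 | 30 | 9.6 | 9.5 | 8.9 | 8.4 | 7.1 |
| one, at 0.98 | 16 | 9.4 | 9.4 | 9.0 | 8.5 | 7.4 |
| one, at 0.53 | 30 | 8.6 | 8.6 | 8.6 | 8.5 | 7.1 |
| one, at 0.53 | 16 | 6.3 | 6.7 | 6.8 | 7.2 | 7.0 |
| two, at 0.53 | 30 | 4.8 | 4.8 | 5.0 | 5.0 | 5.1 |
| two, at 0.53 | 16 | 4.2 | 3.9 | 4.1 | 4.7 | 4.9 |

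With one outcome at 0.98 and n=30 the gate opens in at least 99% of runs, so it screens out almost nothing. If all three outcomes differ, no false claim is possible.

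**4. The remedies.** With one outcome at 0.98 and n=30, Holm gives 3.7 to 4.9% and the full closed test about 3.0 to 4.5%.

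**5. Power for one affected outcome** (0.53, n=30), by correlation:

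| Rule | 0 | 0.3 | 0.5 | 0.7 | 0.9 |
|---|---|---|---|---|---|
| Present rule (%) | 59.9 | 64.8 | 72.1 | 78.3 | 80.1 |
| Holm without the gate (%) | 64.7 | 64.6 | 64.4 | 64.2 | 64.2 |

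Holm after the gate loses about 3 to 16 points against the present rule, rising with correlation. The closed test loses about 0 to 4 points if one or all three outcomes are affected (for example 72.1% to 68.8% at correlation 0.5) and about 8 to 11 points if two are.

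**The case against.** The strongest reply is that the plan claims little. It says the gate is there to help control the risk, it calls the individual tests post hoc, and it discloses that they are uncorrected. The gate does help: with no true effect the error is below 5%, against up to 14.3% without it. Each null outcome's own error also stays near or below .05; only the joint rate rises. All of this is correct, and it means that the rule is weaker than it appears rather than contradictory. It does not answer the point, because no other protection is named for the primary outcomes and, unlike the secondary ones, they are not labelled exploratory.

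A reader might also infer that control fails in the very scenario the sponsor expects: a large 3XF8W effect with the TUG and the Four Square Step Test null. The article does not say so. The 0.98 is given as an example of larger effects. The Results and Expected Findings sections anticipate benefit in side-stepping, turning and other tasks that are not straight walking. If two or three outcomes benefit, there is no excess error. The one-outcome case is a possibility that the procedure ought to cover, not a prediction of the article.

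Nor should the cost of repair be called trivial. Holm after the gate takes power for a single effect of 0.53 from 42% to 29% in the bilateral group at correlation 0.7, and the article already calls that group underpowered.

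**Conclusion.** The concern holds in limited form. The gate controls the familywise error of the three follow-up tests when none of the outcomes differs, and there is no excess when two or three do. When exactly one differs, the error is about 7 to 10% at an effect of 0.98 (either sample size), about 7 to 9% at 0.53 with n=30, and about 6 to 7.5% at 0.53 with n=16.

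To say without conditions that the error nearly doubles would overstate it. The limit of 9.75% is approached only with low correlation and a gate that almost always opens; at correlation 0.9 the error is about 1.4 times nominal.

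The error arises separately in each amputation group. The figures rest on assumed correlations, normal differences and two-sided tests at .05. The calculation itself is secure; which outcomes are truly null is unknown.

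**What to change.** In Primary Outcomes, or in the SAP if it carries the operative text, replace the statement that no correction is made with one of these, applied in each group:

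- **Full closed test.** Claim an outcome only if the MANOVA, both two-outcome multivariate tests that contain it, and its own paired test are all significant at .05.
- **Holm** on the three paired tests, with or without the MANOVA gate.

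Either holds the familywise error at or below about 5%. The closed test usually costs less than Holm after the gate when a single outcome is affected and correlation is high. Holm without the gate is simpler and gives about 64% power for one affected outcome at 0.53 and n=30, whatever the correlation, against 60 to 80% now.

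Restate the section Power for the procedure chosen: its figure of above 80% describes neither the present gated rule in general nor either remedy. Give the correlation assumed, and do this for n=16 as well.

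If the sponsor prefers no correction, state that only the MANOVA is confirmatory and that the individual-outcome tests are exploratory, as the plan already does for the secondary outcomes.

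The change is short and needs no new data. Data collection is expected to run to March 2027 and the statisticians are to be blinded to the condition labels, so the rule can be settled before the final analysis.

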### Satisfaction Measures

Satisfaction (PLUS-M) will be analyzed using paired *t* tests (or Wilcoxon tests) at α=.025 to maintain a familywise error rate of .05 across satisfaction outcomes.

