#### Participant Qualitative Measures

The participant-related outcome measures include a demographic questionnaire and the Prosthetic Limb Users Survey of Mobility (PLUS-M). The PLUS-M is a 12-item questionnaire developed at the University of Washington Center for Outcomes Research in Rehabilitation, which examines typical everyday mobility activities on a 5-point Likert scale. Participants were also asked to fill out a logbook every day during the study. They could complete the logbook on paper or via a digital reminder system sent via email by REDCap.

Semistructured interviews will be completed during research phases B2 (investigational foot) and A2 (usual foot). These interviews will clarify significant events documented in the logbooks. The focus of interviews will be on gathering information about the participants’ experience using different prosthetic feet, with an emphasis on identifying activities that are facilitated or hindered by the functioning of the prosthetic foot.

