## Discussion

### Expected Findings

It is expected that the side-to-side adaptability of the META Arc prosthetic foot will help people with above-knee amputations, people with bilateral amputations, and people with lower levels of mobility manage their everyday activities better. It is expected that the results of this study will demonstrate that people with lower levels of mobility can complete non–straight gait tasks such as turning better and will participate in more challenging activities every day.

It is hypothesized that participants with bilateral amputations will report greater satisfaction, mobility, and comfort when using a prosthetic foot with frontal plane adaptability (unlocked condition) than when wearing a prosthetic foot without frontal plane adaptability (locked), as measured by the PLUS-M. It is also expected that participants will demonstrate improved performance during the 3XF8W using a prosthetic foot with frontal plane adaptability compared to a foot without frontal plane adaptability.

A cutoff for the TUG in determining fall risk of ≥8.17 seconds has been previously determined by Sawers and Hafner [16]. However, it is not clear what part of the TUG is causing the increased risk. By completing component analysis, this study will determine what part of the TUG is causing times above this fall risk threshold.

A previous study of the META Arc foot showed that optimal stiffness for walking on flat surfaces is not the same as for turning [17]. Preliminary findings have shown that there are differences in stride length and swing time when comparing turning with the prosthetic foot on the inside or the outside of the turn. This may have some implications in the development of gait training and fall prevention strategies.

During logbook and interview analysis, it is expected that participants will report their perceived changes in person-specific mobility during activities that require frontal plane adaptability. The logbook and interviews will also provide feedback on the investigational foot regarding what aspects the participants did or did not like. This information will be very useful for making improvements for the next version if needed. Preliminary logbook analysis has shown that participants have engaged in walking on uneven terrain and participated in activities such as walking the dog, hiking, and shopping with benefits while wearing the investigational foot.

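### The PLUS-M is tested at α=.025 in a satisfaction family with no other named member, is described as a mobility scale, and the powered preference comparison has no stated α or analysis

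*Protocol article*

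**What the plan says.** - **The family and its α.** The Satisfaction Measures section of the protocol article says: "Satisfaction (PLUS-M) will be analyzed using paired" t tests, "or Wilcoxon tests) at α=.025 to maintain a familywise error rate of .05 across satisfaction outcomes". No other satisfaction outcome is named there. The Secondary Outcomes section lists PLUS-M subscales among the outcomes tested at α=.05 and treats all secondary results as exploratory.
- **What the PLUS-M is.** Participant Qualitative Measures presents it as a 12-item questionnaire "which examines typical everyday mobility activities on a 5-point Likert scale".
- **What is claimed from it.** Expected Findings hypothesises that participants with bilateral amputations "will report greater satisfaction, mobility, and comfort when using a prosthetic foot with frontal plane adaptability", and gives the PLUS-M as the measure.
- **Preference.** The Power section states: "The study is also powered (81%) to detect a 75% preference for one configuration (vs 50% under the null) using a sign test with n=30". It gives no α and no sidedness. Preference is not listed under Outcome Measures, and none of the analysis sections (Primary Outcomes, Satisfaction Measures, Secondary Outcomes, Logbook and Walkway Data) mentions it. The only sign test in those sections is for fall counts.
- **Other power figures.** The Power section also says: "With n=30 for the above-knee and K2 groups, the study is powered (>80%) to detect a standardized effect size of 0.53", and gives more than 50% for the bilateral group at n=16. The primary MANOVA "will be used to evaluate the effect of foot configuration at α=.05".

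**The concern.** Three things do not fit together.

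1. An equal split of .05 into .025 implies two tests, and only one is named. If the PLUS-M stands alone, the plan gives up power without gaining any protection. If there is a second member, a reader cannot tell what it is. The level at which the PLUS-M is judged could then be argued after the results are seen.
2. The outcome labelled satisfaction is, by the article's own description, a mobility questionnaire. A positive result could be reported as greater satisfaction and comfort when only self-reported mobility was measured. The abstract says results may inform prescription and reimbursement policy, so the label has consequences.
3. A formal power claim is made for a preference test that has no α and no place among the outcomes or analyses. It is unclear whether preference is confirmatory.

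**Working it through.** **Step 1. How many tests does .025 imply?** Two tests at .025 sum to .025 + .025 = .05. One test at .025 has a familywise rate of .025, half of what the section says it maintains. The PLUS-M subscales cannot be the second member, because they are secondary at .05. The three amputation groups do not explain the split either: an equal split over three would be .05/3 = .0167, and the text refers to outcomes, not groups.

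**Step 2. Reproduce the plan's paired-test power.** Inputs from the Power section: standardized effect d=0.53, n=30 and n=16. For a paired t test, the noncentrality is d√n with n−1 degrees of freedom, and two-sided power is P(|T| > critical t).

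| n | d√n | α (two-sided) | critical t | power |
|---|---|---|---|---|
| 30 | 0.53 × 5.477 = 2.903 | .05 | 2.045 | 80.1% |
| 30 | 2.903 | .025 | 2.364 | 70.4% |
| 16 | 0.53 × 4 = 2.12 | .05 | 2.131 | 50.9% |
| 16 | 2.12 | .025 | 2.490 | 38.3% |

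The .05 rows match the stated >80% and >50%, so the Power section works at two-sided .05. The .025 rows show what the PLUS-M test would have at the same effect size. The article states no power for the PLUS-M, so these rows contradict no stated figure; they show the cost of the halved α.

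**Step 3. Reproduce the 81% for preference.** Inputs from the Power section: n=30, 75% against 50%, sign test.

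- Exact binomial, two-sided .05: reject at 21 or more of 30. Size is 2 × .02139 = .0428, and power is P(X ≥ 21 | .75) = 80.3%.
- Normal approximation, two-sided .05: (0.25√30 − 1.960 × 0.5)/√(0.75 × 0.25) = (1.369 − 0.980)/0.433 = 0.899, which gives 81.6%.

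Both are close to 81%. A one-sided exact test at .05 gives 89.4% and does not fit. A one-sided exact test at .025 has the same cut-off of 21 (size .0214) and so the same 80.3%.

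**Step 4. The same test at two-sided .025.** Reject at 22 or more of 30. Size is 2 × .00806 = .0161, and power is 67.4% exact (71.7% by the normal approximation). This applies only if preference belongs to the .025 family.

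**Step 5. Preference at n=16.** The exact cut-off is 13 at both levels (two-sided size .0768 at 12 and .0213 at 13), so power is 40.5% at .05 and at .025 alike. The split costs nothing here; sample size is the limit. The article claims preference power only for n=30.

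**Step 6. Construct.** Set side by side, Participant Qualitative Measures assigns one construct to the PLUS-M (everyday mobility), Satisfaction Measures assigns another (satisfaction), and Expected Findings assigns three (satisfaction, mobility and comfort). Only mobility is common to the description of the instrument and the hypothesis.

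**The case against.** The strongest reply is that this is a condensed article. The plural in Satisfaction Measures may be the trace of a longer list, and the study-procedure sections mention unnamed questionnaires and subjective ratings that could supply a second member. Testing a sole member at .025 is conservative and inflates no error. The PLUS-M is not a primary outcome, and mobility is one of the three constructs in the hypothesis. The Power section does give preference a test, a null, an alternative and an n, and an interview compares the two configurations.

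Much of this stands, and it limits the point. A reader might infer that preference is the missing second member and that the 81% is therefore wrong. The article does not support that. It never places preference in the family, and the family's stated methods are paired t or Wilcoxon tests, whereas preference has a sign test. If preference lies outside the family, 81% at two-sided .05 is correct. Nor can one say that 81% holds only at .05, since sidedness is not stated and one-sided .025 gives the same power.

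Condensation does not remove the rest. The article itself states an α split with one named outcome, uses as satisfaction an instrument it describes as mobility, and makes a power claim for a test that it gives no α and does not place among its analyses. The interviews are analysed thematically, so they do not supply the missing test.

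**Conclusion.** The concern holds at moderate severity.

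- **PLUS-M α.** As written, a single test at .025 uses half the stated familywise rate. At d=0.53, this lowers power from 80% to 70% at n=30 and from 51% to 38% at n=16. The bilateral group, for which the PLUS-M hypothesis is stated, is the n=16 group. These figures assume a two-sided paired t test and borrow the plan's 0.53, which the article does not tie to the PLUS-M.
- **PLUS-M label.** On the article's own description, a PLUS-M difference supports a claim about self-reported mobility, not about satisfaction or comfort.
- **Preference.** The comparison lacks an α and a place in the outcomes and analysis. Its 81% is consistent with two-sided .05. The fall to about 67% is conditional on a two-sided .025 test within this family.

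The three primary performance outcomes and their MANOVA are not affected.

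**What to change.** 1. State the members of the family. If the PLUS-M is the only one, test it at .05. If there is a second, name it and use Holm (smaller p value against .025, then the other against .05) in place of a fixed .025 each. Holm keeps the .05 familywise rate and is never less powerful than the fixed split.
2. Call the PLUS-M self-reported mobility in Satisfaction Measures and Expected Findings, and rest satisfaction and comfort claims on other data, such as the logbook and interviews.
3. Either say how preference is recorded, place it in the analysis with its α and sidedness, and restate its power at that α, or delete its power claim. At n=30, two-sided, that is about 80% at .05 and 67% at a fixed .025; within a two-member Holm procedure, 67% is a lower bound.

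The α and label changes are wording only. They can be made before analysis, since data collection is expected to run to March 2027. Keeping preference as a formal outcome costs nothing more only if a preference response has been recorded so far. The article does not show this, and 66 participants had completed the study by September 2025.

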### Power

With n=30 for the above-knee and K2 groups, the study is powered (>80%) to detect a standardized effect size of 0.53. In the bilateral group (n=16), the power is greater than 50% for the same effect size. Preliminary data show larger effects (eg, 0.98 for the 3XF8W), supporting adequate power. Although underpowered to detect a meaningful difference in the bilateral group, 16 subjects is in line with other gait studies that have published data on 10 [13], 15 [14], or 19 [15] subjects with bilateral amputations, a challenging population to recruit and enroll. The study is also powered (81%) to detect a 75% preference for one configuration (vs 50% under the null) using a sign test with n=30. Although no minimal clinically important difference has been established, it is predicted that a standardized effect of at least 0.50 will correspond to an impactful improvement in participants’ physical function.

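### The stated power matches a single paired t test, not the three-outcome MANOVA that gates the primary analysis, whose power depends on a correlation and an effect pattern that are not given

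*Protocol article*

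**What the plan says.** All three statements are in the protocol article.

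- **Primary analysis (Primary Outcomes).** There are three outcomes: "Primary performance outcomes include the TUG, the 3XF8W, and the Four Square Step Test". On these, "a multivariate analysis of variance (MANOVA) will be used to evaluate the effect of foot configuration at α=.05", with a permutational version if assumptions fail. The paired tests are conditional: "pairwise comparisons of the primary outcomes will only occur if the multivariate difference comparison from the MANOVA is significant". The Statistical Analysis section has every analysis done separately by amputation group, so the working sample sizes are 30, 30 and 16.
- **Power (Power).** "With n=30 for the above-knee and K2 groups, the study is powered (>80%) to detect a standardized effect size of 0.53". Then: "In the bilateral group (n=16), the power is greater than 50% for the same effect size". No test, alpha or correlation between outcomes is attached to these figures. The section also says: "Preliminary data show larger effects (eg, 0.98 for the 3XF8W), supporting adequate power".
- **Size of a worthwhile effect (Power).** No minimal clinically important difference is established, but "it is predicted that a standardized effect of at least 0.50 will correspond to an impactful improvement in participants’ physical function". The section concedes that the bilateral group is underpowered.

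**The concern.** Under the article's own rule, a paired t test on a primary outcome never stands alone. It runs only after a significant MANOVA. A power figure for a lone t test therefore describes an analysis that the trial does not perform on its primary outcomes.

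A single standardized effect does not fix the power of a three-outcome test either. One also needs to know how many outcomes shift, by how much, and how their within-person differences correlate.

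What is at stake is interpretation. If the MANOVA is not significant in a group, readers will weigh that against the published >80% or >50%. Depending on inputs that the article does not give, the real figure could be well above or well below it.

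**Working it through.** **Inputs from the article.** n=30 (above-knee and K2) and n=16 (bilateral); standardized effect d=0.53; three outcomes; α=.05; the MANOVA gate; separate analysis by group.

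**Assumptions.** Two-sided t tests; complete pairs; normal differences; MANOVA applied to the paired differences; a common correlation r between the three differences. The article gives no r, so a range is shown.

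**Step 1: reproduce the stated figures.** One paired t test has df = n−1 and noncentrality d√n.

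- n=30: 0.53 × √30 = 2.90, critical value 2.045, power 80.1%.
- n=16: 0.53 × √16 = 2.12, critical value 2.131, power 50.9%.
- The effect that gives exactly 80% at n=30 is 0.529, the article's 0.53.

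Other candidates fit less closely (n=30 / n=16):

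- normal approximation: 82.7% / 56.4%
- one-sided .05: 88.3% / 64.7%
- α=.025: 70.4% / 38.3%
- α=.05/3: 64.2% / 31.8%

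**Step 2: power of the MANOVA gate.** With two conditions per person, this is the one-sample Hotelling T² test on three differences. It uses F(3, n−3) with noncentrality n·D².

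- All three outcomes shift by d: D² = 3d²/(1+2r).
- Only one shifts: D² = d²(1+r)/[(1−r)(1+2r)].

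At d=0.53 and r=.5, both give D² = 0.421, so the noncentrality is 30 × 0.421 = 12.6 or 16 × 0.421 = 6.7.

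| Gate power at 0.53 | r=0 | .3 | .5 | .7 | .9 |
|---|---|---|---|---|---|
| n=30, all three shift | 98% | 89% | 80% | 72% | 64% |
| n=30, one shifts | 61% | 68% | 80% | 95% | >99% |
| n=16, all three shift | 76% | 54% | 44% | 37% | 33% |
| n=16, one shifts | 31% | 35% | 44% | 65% | 99% |

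If all three shift, the >80% claim holds for r below about 0.50 and the >50% claim for r below about 0.37. At r=.5 the gate happens to give 80% at n=30, but only 44% at n=16.

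**Step 3: passing the gate and then declaring a given shifted outcome.** This is P(MANOVA significant and t significant). It cannot exceed P(t significant), so it is capped at 80.1% and 50.9%. Simulation with 10,000 replicates per cell (standard error about half a percentage point) gives:

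| Gate plus t at 0.53 | r=0 | .3 | .5 | .7 | .9 |
|---|---|---|---|---|---|
| n=30, all three shift | 79% | 77% | 72% | 68% | 62% |
| n=30, one shifts | 60% | 65% | 72% | 79% | 80% |
| n=16, all three shift | 46% | 38% | 35% | 31% | 29% |
| n=16, one shifts | 27% | 31% | 34% | 43% | 51% |

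**Step 4: reference figures at 0.50.** A single paired t test gives 75.4% (n=30) and 46.5% (n=16). The gate at r=.5, under either pattern, gives 75% and 40%.

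**The case against.** **The figures are not miscalculated.** This stands: they are right for a single paired t test. That this test lies behind them is an inference, because the section names none. The inference is strong, since both powers and the 0.53 itself agree with it.

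**A condensed article may leave the test and the correlation to a fuller document.** It may, and leaving them out would be no fault by itself. What remains is that two stated parts of the article do not fit together: the power figures and the gate.

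**The MANOVA can have more power than the t test.** This stands. A reader might infer that the stated power is always too high, and the documents do not support that. At n=30 the gate exceeds 80% when all three outcomes shift and r is below about .5, or when one shifts and r is above about .5. Only the gate-plus-t figure is capped by the t test. Its loss ranges from almost nothing to about 20 points at n=30, and the article names no single outcome as decisive.

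**The preliminary effect of 0.98 leaves ample room.** In part. If only the 3XF8W shifts by 0.98, gate power is at least 99% at n=30 and about 82% or more at n=16 for r from 0 to .7. But 0.98 is given for one outcome, and no effects are given for the other two. It also does not turn the claim made at 0.53 into a claim about the MANOVA.

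**The value 0.50 is not a design target.** This stands. A reader might infer that the trial fails its own threshold, because the t test has 75.4% there. The article only predicts that effects of that size matter, and never claims 80% power at 0.50.

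**Low power in the bilateral group is already conceded.** This also stands, and that group needs no new label. The figure attached to the concession is still the t-test value.

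**Conclusion.** The point holds as a mismatch between the power statement and the primary analysis. The >80% and >50% figures match a lone two-sided paired t test at α=.05, whereas each group's primary conclusion rests on a three-outcome MANOVA. Over the patterns examined, with r up to .9 when all three outcomes shift and up to .7 when only one does, gate power at 0.53 is 61% to 98% for n=30 and 31% to 76% for n=16. Over both patterns with r from 0 to .9, gate-plus-t power is about 60% to 80% and 27% to 51%.

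These ranges rest on assumed correlations, two simple effect patterns and normal paired differences. They show how far the answer moves, not what the trial's power is. The direction of the discrepancy for the gate cannot be determined from the article.

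This should be fixed, but it is not critical: type I error, conduct and the analysis itself are untouched.

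**What to change.** Rewrite the Power section as follows.

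1. Name the test, sidedness and alpha behind 0.53.
2. Replace the unqualified >80% and >50% claims with MANOVA gate power at n=30 and n=16, over a stated range of correlations and effect patterns.
3. Beside it, give the power to pass the gate and then declare a given outcome.
4. Add the figures at 0.50 for reference (single paired t test: 75.4% at n=30 and 46.5% at n=16), without presenting 0.50 as a design target.
5. Say that the 0.98 preliminary effect concerns the 3XF8W only.

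The revised text should not say that the original power was too high in every case.

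The cost is text only, with no added participants and no change to the analysis. The price is that the power figures become conditional and mostly less favourable than those now stated.
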